### Outcomes

Poor clinical outcomes for RCT1 [21] are death at any time from randomisation up to day 15 of initiation of treatment, any sign of critical illness (*i.e.* no movement at all, unable to feed at all, or convulsions) or any sign suggestive of another serious infection (*e.g.* meningitis, bone or joint infection on day two, four, or eight post-randomisation, any new CSI sign on day four or eight post-randomisation, or persistence of the presenting CSI sign on day eight post-randomisation).

Poor clinical outcomes for RCT2 [22] are death between randomisation (day three of initiation of therapy) and day 14 of initiation of therapy, presence of any sign of critical illness (*i.e.* no movement at all, unable to feed at all, or convulsions) or any sign suggestive of another serious infection (*e.g.* meningitis, bone or joint infection on day four and eight of initiation of therapy, or presence of any sign of CSI on day eight of initiation of therapy).

The effectiveness rates will be estimated for each treatment arm for both RCTs as the proportion or percentage of the population that did not experience poor clinical outcomes. The following formula is used:

Mean effectiveness rate (E) = (positive outcomes (O) / total population (N)) × 100

Where O is the number of individuals with positive outcomes calculated as O = N − P, N is the total number of individuals in each arm of the treatment group, and P is the number of individuals who experienced poor clinical outcomes (*e.g.* death, deterioration, or other conditions described above) among N. Mean effectiveness will vary between enrolled SYI and those who received recommended treatment, as P and N would differ. The effectiveness measure (‘proportion without poor clinical outcomes’) is chosen for its direct alignment with trial endpoints and feasibility across heterogeneous sites.

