Coverage of sick YIs (SYI) assessed, enrolled and treated under both RCT1 and RCT2 for control and intervention.Data on two outcome variables for all SYI covered under different treatment arms. Well-trained independent outcome assessor visits all enrolled cases on days two (only for RCT1), four, eight, and 15 after the initiation of treatment to assess the study outcomes in both intervention and control arms.Average annual salaries of nurses, paediatricians, medical officers and any other staff supporting treatment. To calculate staff costs per minute, data will be collected on the average number of days in a month and the average number of hours in a day that staff work.Staff time will be considered only for activities that are linked to hospital staff and not those linked to research staff, such as outcome assessment or treatment documentation (**Table 1**, **Table 2**). The activities for the staff time will be based on a pre-defined implementation strategy [21,22].Data will be collected for SYI that receive at least 80% of the treatment (recommended treatment) and those who receive <80% of seven-day (<5.5 days) treatment (partial treatment). The latter occurs due to a treatment failure, a change in treatment, readmission, left voluntarily, or death. For the recommended treatment, we will collect costs for the seven-day treatment period following the initial assessment, across both study arms and both trials. For partial treatment, medical costs will be calculated for an average treatment period of three days in RCT1 after the initial assessment, and for two days in RCT2 in both inpatient and outpatient arms after randomisation. Costs for enrolled SYI will be weighted by the proportion of participants receiving 80% recommended treatment and those receiving partial treatment, with weights set to SYI for each group. This prevents any child randomised and enrolled from being missed. Costs due to complications, changes in treatment, and/or readmission are outside the seven-day recommended treatment window in both study arms of both trials and will not be collected.Data on staff time per visit for an activity and the number of visits undertaken for each activity during the recommended treatment period will be collected by interviewing at least 3–5 staff of each type at each hospital.The staff time for all visits during the treatment period will be weighted by the number of days an infant receives the activity and the number of YI receiving the activity (defined as weighted by infant days). For the first activity assessment on presentation at the hospital, the number of SYI will be all enrolled for a given treatment, whether partial or recommended. For all other activities, SYI who receive 80% recommended treatment will be considered to have received seven days of treatment, and those receiving partial treatment for an average of three days to calculate the costs for those enrolled.The average exchange rate used to convert all the cost estimates in local currency into USD will be for 2024, the period for which the salaries of providers, prices and household costs will be reported. It will ensure consistency, and inflation rate adjustments will not be needed for cost calculations. The recommended treatment period will be seven days for inpatient treatment in the control arm and seven days for outpatient treatment in the intervention arm for RCT1. For RCT2, the average length of inpatient treatment is 48–72 hours, prior to a negative CRP laboratory test. In RCT2, the control group after randomisation will continue receiving inpatient care for five days, while the intervention group will be discharged from the hospital on oral amoxicillin for five days to be taken at home. Both arms will share the initial hospitalisation costs during the first two days in RCT2, including CRP test costs (including staff time, kits, and laboratory costs).The data on quantities used of injection gentamicin, injection ampicillin and oral amoxicillin will be as per the recommended treatment and partial treatment per SYI for each treatment arm under each RCT.The number of SYI receiving specific medicines and consumables for each arm under both RCTs will be calculated based on the numbers receiving recommended treatment and those receiving partial treatment.Information on types and quantities of consumables required with each medicine will be collected separately for each hospital and each arm under both RCTs. The cost of medicines and consumables will be charged per size in which they are dispensed. Medicine dosage varies with the weight of the YI [21,22]. Price will be taken for full strength, and the rest will be marked as wastage. Price data will be taken from the hospital's pharmaceutical department (if available); otherwise, the market price or the WHO price will be used.Data on annual financial expenditures and admissions in the newborn intensive care units or paediatric wards where YI with PSBI are treated as inpatients at the hospital will be collected and allocated based on patient days to calculate the inpatient bed costs/ SYI treated as an inpatient. These expenditures include administration, utilities, laundry, security, data management, internet, non-consumables and other costs in the hospital inpatient ward.Hospital ambulance to transport enrolled SYI under a specific treatment arm is a cost to the hospital. It is difficult to get this information separately for each enrolled SYI under different treatment arms from the hospital data. Indirect estimation based on the average trip cost and the number of SYI using free public ambulances, estimated from household data for each treatment arm in RCT1 and RCT2, will be used.Hospital data will also be collected for operational costs, which help to strengthen the assessment, identification, and treatment of SYI with PSBI. These include training, supplies, and communication. The total costs under these three will be estimated per SYI assessed. Staff training costs include the costs of development of training material and training cost per staff per day based on the per diems, honorarium for trainers, venue and refreshment costs. Total training costs will be calculated for all staff who were used to assess and treat SYI and will be estimated per SYI assessed. Training costs for research staff for outcome assessment or data collection will not be collected or included. Price and quantities of supplies used during the assessment, such as timers, thermometers and weighing scales, will be prorated for PSBI assessed. Communication costs, include job aids or educational material, and the cost of videos developed and played at the hospitals for educating the mothers about the danger signs. Data will be collected on item quantities and prices from hospitals to assess total costs and costs per SYI assessed.

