### CEA

CE will be evaluated by estimating the ICER, defined as the difference in mean costs between the intervention and control arms divided by the difference in effectiveness between the two arms: ICER = (C_1_ − C_2_) / (E_1_ − E_2_), where C_1_ are the average costs for the intervention group; C_2_ are the average costs for the control group; E_1_ is the mean effectiveness measure for the intervention group, and E_2_ is the mean effectiveness measure for the control group. We will use societal costs – hospitals and households’ – medical costs (staff time, medicines, consumables); hospital inpatient bed cost, operational costs and households’ non-medical costs (transport, food and wage loss) for ICER calculations for all randomised SYI in both arms. We will also report ICER from only the provider/payer perspective using only medical costs for all enrolled SYI and those receiving at least 80% of the recommended seven-day treatment as a sensitivity analysis [27].

For RCT2, while the baseline costs will be presented for both pre- and post-randomisation for both study arms, the costs for ICER calculations will be compared only post-randomisation.

For each RCT, cost measures will be evaluated in both the control and intervention arms for all enrolled infants who receive either the full seven-day treatment or partial treatment. Effectiveness will be assessed in the same population based on clinical outcomes recorded on days two (for RCT1), four, eight, and 15 following treatment initiation. The ICER will be calculated for each RCT to assess whether the intervention is more cost-effective than the control.

There can be 4 case scenarios for ICER (**Figure 2**):

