### Site-wise and combined analysis plan

While site-wise analyses will provide insights into differences across study sites, results will also be presented for all sites combined and separately for the Asia and Africa regions. Variations in care pathways will be addressed through hospital-level stratification of staff, medicine, and consumable costs, using infant-days as weights to derive site averages. Costs for partial treatment will be estimated at the hospital level by using infant-days as weights for infants receiving partial treatment. Overall costs for enrolled infants will be estimated at the site level using the weighted average of those receiving recommended treatment and those receiving partial treatment. The combined average across all sites will be estimated by using enrolled infants at each site as weights for each treatment arm. The number of infants receiving at least 80% of the recommended treatment in each treatment arm will be used as weights to estimate the combined average hospital costs for the recommended treatment across all sites.

Average weighted inpatient bed costs at the site level will be estimated across all hospitals for each treatment arm using the number of SYIs enrolled in paediatric and newborn wards as weights. Combined inpatient bed costs will then be estimated using the total number of SYIs enrolled in these wards as weights at each site. Average operational costs will also be stratified at the hospital level within each site by using the number of SYIs assessed as weights, and site-stratified for combined analyses using the number of SYIs enrolled as weights at each site.

Average household costs – including registration, food, transport, and wage loss per SYI – will be calculated at the site level using the household survey sample size as the denominator. For pooled analyses, enrolled SYIs will be used as weights across sites. Both the median and the arithmetic mean will be reported to describe the distribution of costs for each variable. Uncertainty in CE will be presented using site-level, regional-level, and pooled ICERs plotted on CE planes. In addition, the mean INB will be estimated and pooled across sites, and 95% confidence intervals will be derived using the *t*-distribution based on site-level variation. An INB greater than zero will indicate that the intervention is cost-effective at the specified willingness-to-pay threshold.

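### The ICER in infants with at least 80% of treatment selects partly on the outcome it measures, so its bias has unknown direction and it says little about robustness

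*Protocol article*

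**What the plan says.** All references are to the protocol article.

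- **Population of the analysis.** The CEA section bases the main societal ICER on all randomised infants. It adds a provider/payer ICER for all enrolled infants and for "those receiving at least 80% of the recommended seven-day treatment as a sensitivity analysis".
- **Why infants fall below 80%.** The Hospital data section calls less than 80% of the seven-day course (given as under 5.5 days) partial treatment, and explains: "The latter occurs due to a treatment failure, a change in treatment, readmission, left voluntarily, or death".
- **Effectiveness measure.** The Outcomes section defines it as "the proportion or percentage of the population that did not experience poor clinical outcomes", that is (N − P)/N with P the number of poor outcomes, and adds: "Mean effectiveness will vary between enrolled SYI and those who received recommended treatment, as P and N would differ".
- **Timing of poor outcomes.** In RCT1 they include "death at any time from randomisation up to day 15 of initiation of treatment" and "persistence of the presenting CSI sign on day eight post-randomisation". In RCT2 they include death up to day 14 and any sign of clinically severe infection on day eight.
- **Pooling of costs.** For recommended-treatment hospital costs, the Site-wise and combined analysis plan states: "The number of infants receiving at least 80% of the recommended treatment in each treatment arm will be used as weights". Costs for all enrolled infants are instead pooled with enrolled numbers.

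**The concern.** Whether an infant reaches 80% of treatment is settled after randomisation. Death is itself a poor outcome, and treatment failure, change of treatment and readmission will often follow from the signs that count as one. Restricting to 80% or more therefore conditions partly on the result being compared. In open-label trials of home against hospital care, the timing of detected failure and the reasons for leaving may well differ between arms, so the distortion need not cancel.

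The stake is interpretation. The Hypothesis/objective section links the RCT2 conclusion to non-inferior outcomes together with lower costs. A sensitivity ICER close to the main one would be read as reassurance, and a different one as a warning. Neither reading would be safe. The incremental net benefit does not cure this, because it uses the same effect difference.

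The weighting rule is a separate problem in the same analysis. Randomisation can be expected to give the arms a similar enrolled site mix, but not a similar site mix of completers. A pooled cost difference can therefore reflect different country mixes.

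**Working it through.** The article gives no event rate and no share of partial treatment, so there is no plan figure to reproduce. All values below are assumptions for illustration.

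**Effect difference.** In each arm let

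- p = risk of a poor outcome (assumed 8% intervention, 6% control)
- f = share of poor outcomes in which treatment stopped below 80%
- l = share of infants without a poor outcome who still stopped below 80%, for example by leaving

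Among all randomised infants, E = 1 − p. In the 80% set, E80 = (1 − p)(1 − l) / [(1 − p)(1 − l) + p(1 − f)]. The all-randomised difference is 92% − 94% = −2.00 points.

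Equal f, with l = 0, showing the poor-outcome risk that remains in the set:

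- f = 0.5: 0.04/0.96 = 4.17% against 0.03/0.97 = 3.09%, a difference of 1.07 points
- f = 0.8: 0.016/0.936 = 1.71% against 0.012/0.952 = 1.26%, a difference of 0.45 points

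With l = 2% in both arms:

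| p (int./control) | f (int./control) | Difference in all randomised | Difference in 80% set |
|---|---|---|---|
| 8% / 6% | 0 / 0 | −2.00 | −2.03 |
| 8% / 6% | 0.5 / 0.5 | −2.00 | −1.09 |
| 8% / 6% | 0.9 / 0.9 | −2.00 | −0.23 |
| 8% / 6% | 1 / 1 | −2.00 | 0.00 |
| 8% / 6% | 0.5 / 0.9 | −2.00 | −3.60 |
| 8% / 6% | 0.9 / 0.5 | −2.00 | +2.27 |
| 7% / 7% | 0.5 / 0.9 | 0.00 | −2.94 |
| 7% / 7% | 0.9 / 0.5 | 0.00 | +2.94 |

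With equal f, the difference shrinks roughly by the factor 1 − f. With unequal f, it grows, reverses or is created. Different leaving alone also matters: f = 0.5 in both arms with l = 2% (intervention) and 15% (control) gives −0.63 instead of −1.09.

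**ICER.** At an assumed cost difference of −50 USD and l = 2%, the saving per additional poor outcome is about 2,460 USD at f = 0, 4,570 at f = 0.5 and 21,500 at f = 0.9. At f = 0.9/0.5 the effect difference turns positive. The same data would then move from the south-west quadrant to the south-east, and the intervention would appear dominant.

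**Site weights.** Assume two sites with 500 infants per arm each, control cost 50 and 200 USD, and intervention cost 20 and 60 USD. Control completion is 90% and 60%; intervention completion is 95% at both sites.

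- Control, completer weights: (450 × 50 + 300 × 200)/750 = 110 USD. Equal weights: 125 USD.
- Intervention: 40 USD either way.
- Saving: 70 USD with completer weights, 85 USD with common weights.

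With control completion of 90% and 80%, the control mean is (450 × 50 + 400 × 200)/850 = 120.6 USD and the saving 80.6 USD.

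**The case against.** The strongest reply is that the main inference is protected. The societal ICER uses all randomised infants, a provider/payer ICER uses all enrolled infants, and partial-treatment infants are weighted into enrolled costs. The article also recognises that small effect differences make an ICER unstable, and adds the incremental net benefit. This stands, and it confines the problem to one sensitivity analysis.

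A reader might infer more: that the 80% set removes poor outcomes by definition, that it must show close to 100% effectiveness in both arms, and that it drives the difference to zero and makes the ICER explode. The article does not support this:

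- Day-eight signs, and deaths up to day 15 (RCT1) or day 14 (RCT2), can occur after the 80% point and then stay in as poor outcomes.
- Voluntary leavers without a poor outcome are also removed, and the five listed reasons carry no proportions.
- Shrinkage needs similar early-stopping shares in the two arms, and a zero difference needs every poor outcome to stop treatment early.

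A third reply is that the Statistical analysis procedures section uses outcomes of all enrolled infants for the ICERs. If that also governed this analysis, completers' costs would be divided by an effect from a different population, which is no better.

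On weights, completer counts do give the ordinary mean cost among completers, and the 70 against 85 USD example uses strong contrasts. Site-wise results and site-level net benefits do not mix sites. Both points are fair, and they limit the weighting problem to the pooled recommended-treatment costs.

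**Conclusion.** The concern holds in limited form. The 80% ICER is selected on a post-randomisation event that is partly the outcome itself, and the bias has unknown direction. Under the assumed 8% and 6% risks, a true 2.0-point difference could appear as about 1.1 or 0.45 points with equal early-stopping shares of 50% or 80%. With shares of 0.5 and 0.9 in the two arms (and 2% leaving) it could appear as 3.60 points in the same direction or 2.27 in the opposite one. These sizes rest entirely on assumed rates. The selection itself follows from the article's own definitions.

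The all-randomised and all-enrolled ICERs are not affected by the 80% selection. The harm is that a comparison offered as a sensitivity analysis could falsely reassure or falsely alarm. The completer weights can add a site-mix difference to its pooled costs. This should be changed, but it does not threaten the main result.

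**What to change.** 1. Define the adherent set as infants who received at least 80% of the treatment due up to failure, death or end of course. Failures and deaths on assigned treatment then stay in as poor outcomes, with the partial-treatment costs already planned. Infants who left before completing, for reasons unrelated to outcome, are excluded.
2. First, the sponsor should confirm that the reason and timing of stopping are recorded per infant. The article names the reasons but does not show that they are held at that level, and it costs partial treatment at fixed average durations (three days in RCT1, two days after randomisation in RCT2). If they are not recorded, keep the present set but label its ICER descriptive and not a robustness check.
3. Pool recommended-treatment costs with the same site weights in both arms (total enrolled per site, both arms together).

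Data collection has ended, so these are analysis-stage changes only. The cost is some extra analysis work and some judgement in classifying reasons for stopping. In open-label trials that classification is best fixed in writing before outcomes are compared by arm. Even then the redefined set is not a fully randomised comparison, since leaving may still relate to outcome, so the all-randomised ICER should continue to lead.

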**Figure 2 F2:**
[figure not shown]
Incremental cost-effectiveness ratio quadrants.

If C_1_ < C_2_ and E_1_ > E_2_, the ICER is negative and falls in the south-east quadrant of the CE plane. In this case, the intervention is less costly and more effective, indicating that the intervention dominates the control.If C_1_ > C_2_ and E_1_ < E_2_, the ICER is negative and falls in the north-west quadrant of the CE plane. In this situation, the intervention is more costly and less effective, indicating that the control dominates the intervention.If C_1_ > C_2_ and E_1_ > E_2_, the ICER is positive and falls in the north-east quadrant of the CE plane. Here, the intervention is more costly but also more effective. The decision regarding CE depends on the CE threshold, which may vary across countries or health systems.If C_1_ < C_2_ and E_1_ < E_2_, the ICER is positive and falls in the south-west quadrant of the CE plane. In this case, the intervention is less costly but also less effective. Decisions about adoption may depend on policy considerations, such as whether a lower-cost intervention could be implemented at a larger scale to improve overall coverage and population-level effectiveness.

ICER values with negative signs are generally easier to interpret. Values in the southeast quadrant indicate that the new treatment is more effective and less costly than the existing treatment. Conversely, ICER values in the northwest quadrant indicate that the existing treatment dominates the new intervention. Positive ICER values in the southwest quadrant may suggest a cost-minimisation trade-off, but these results should be interpreted with caution, as the intervention is associated with reduced effectiveness.

In addition to ICER, we will estimate INB for each site and combined to support the interpretation of CE results [28–30]. INB are useful for quantifying uncertainty in CE, especially when differences in effectiveness are small (making ICER unstable) or when ICER results are inconclusive. For each site, incremental cost Δc = (C_1_ − C_2_) and incremental effect Δe = (E_1_ − E_2_) between intervention and control will be estimated, and INB will be calculated as λ (Δe) − Δc, where λ represents the willingness-to-pay threshold.

